## Outcome measures

### Primary outcome measures

Overall psychological wellbeing will be assessed using two measures, the *General Health Questionnaire* (GHQ-12) and the *Satisfaction with Life scale* (Table 2). The *GHQ-12* is a 12-item self-report questionnaire most widely used to assess levels of psychological distress and to screen for minor psychological disorders [60]. The GHQ has been widely validated and shown to be highly reliable, with a reported Cronbach’s *a* in the range of 0.82–0.90 [61].

**Table 2 Tab2:** Primary and secondary outcomes and data collection

Outcomes	Method of collection	Assessment	Baseline (t0)	Post Intervention (t1)	6-month follow-up (t2)
Primary outcome	Increased wellbeing	General Health Questionnaire (GHQ-12)	x	x	x
		Satisfaction with Life scale	x	x	x
Secondary outcomes	Self-esteem	Rosenberg Self-Esteem Questionnaire	x	x	x
	Career self-efficacy	Career Self Efficacy Questionnaire	x	x	x
	Resilience	Brief Resilience Scale	x	x	x
	Hopefulness	State Hope Scale	x	x	x
	Perceived progress towards the labour market^a^	Cantril’s Self-Anchoring Ladder^a^			x
	Re-employment or labour market participation			x	x
	Re-employment quality	Job satisfaction		x	x
		Job sustainability		x	x
		Level of earnings		x	x
	Access to education / vocational training			x	x

^a^Perceived progress towards the labour market is collected by the guidance practitioner during the intervention/ usual service, at a minimum of two time points, i.e. first appointment and last appointment

The *Satisfaction with Life scale* is a five-item self-report questionnaire developed to measure global cognitive judgemental aspects of life satisfaction [62]. Life satisfaction has been identified as the cognitive judgemental component of subjective wellbeing where judgements of satisfaction are dependent on a comparison with a person’s own standard as opposed to a criterion set within the scale or in a particular domain [62].

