Practitioners to whom intervention clients are referred, are required to complete an in-depth profile for each participant relating to education, previous employment, skills, values, perceived employability and barriers to progression. These data will be held by the practitioner until the intervention is complete. All practitioners are required to administer the ‘P*erceived progress towards the labour market’* measure, Cantril’s Ladder, at baseline and post intervention, although some practitioners may choose to administer this on a more regular basis.

A small token in the form of a voucher is offered to each participant to help increase participation and to thank participants for their time in completing questionnaires at post intervention and at six-month follow-up.

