#### Statistical methods/analysis

The null hypothesis states that there will be no difference between the two groups in terms of primary outcomes (wellbeing) and secondary outcomes (self-esteem, career self-efficacy, resilience, hopefulness, perceived progress toward the labour market) at post intervention and at six-month follow-up. Descriptive statistics will be used to describe the pre-treatment characteristics of participants. Baseline analysis will be conducted to establish the internal consistency of the outcome measure scales, where a Cronbach’s alpha of above 0.7 will be required. Previous studies have reported Cronbach’s alphas of at least 0.7 across all measures*.*

The study will use a randomisation technique (the SNOSE [sequentially numbered opaque sealed envelopes] method as described by Doig and Simpson [74]) which ensures that participants from both groups come from the same population. Pre-treatment analysis will be conducted on primary and secondary outcome measures to show, for example, levels of wellbeing (primary outcome) as indicated by GHQ-12 scores in comparison with appropriate established norms *(e.g. national wellbeing data, HRB (2008))* so as to indicate how job-seekers present for activation services.

Mixed Model Repeated Measures (MMRM) will be used to investigate the effects of the intervention on primary and secondary outcome measures (i.e. wellbeing and employability). Continuous outcome data, including the primary outcome measure of wellbeing and five of the eight secondary outcomes which have been shown to contribute to mental health and increased employability (i.e. resilience, career-efficacy, hopefulness, self-esteem, perceived progress towards the labour market) will be analysed using MMRM. Where parametric test assumptions fail significantly, then non-parametric tests will be used.

MMRM will be used to investigate effects at two between (intervention and control) and three within (pre-intervention, post-intervention and six-month follow-up) levels. Initial MMRM analysis will control for age as a fixed co-variate, along with gender, and duration of unemployment or highest educational level, as applicable. Modelling for the primary outcome will be conducted using an unstructured repeated measures co-variance matrix and all other variables as fixed effects.

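### The collection schedule for perceived progress (Cantril's Ladder) contradicts itself, supplies no pre-randomisation value, and does not support the three-level MMRM planned for it

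*Protocol article*

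**What the plan says.** Four places in the protocol article fix when the ladder is measured or how it is used.

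- **Statistical methods/analysis.** The null hypothesis covers "perceived progress toward the labour market) at post intervention and at six-month follow-up". The ladder is one of five secondary scales in the list "resilience, career-efficacy, hopefulness, self-esteem, perceived progress towards the labour market) will be analysed using MMRM", and the model has "three within (pre-intervention, post-intervention and six-month follow-up) levels".
- **Table 2, cells.** In the ladder row the t0 and t1 cells are empty and the only mark is under the 6-month follow-up (t2).
- **Table 2, footnote to the same row.** The ladder "is collected by the guidance practitioner during the intervention/ usual service, at a minimum of two time points", specified as first and last appointment.
- **Data collection methods.** All practitioners administer it "at baseline and post intervention, although some practitioners may choose to administer this on a more regular basis". T2 is not mentioned.

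The section on the control group adds that case officers use the ladder at the first appointment and again at Activation Review Meetings. Both are timed by PEX class.

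**The concern.** A repeated-measures model with baseline, T1 and T2 levels needs a measurement tied to each level in both arms. It also needs the first level to precede randomisation if change from it is to be read as an effect of assignment. The other four scales in the MMRM list meet this: Table 2 marks them at all three points, and the researcher gives the baseline questionnaire before assignment. The ladder follows a different route, through the practitioner delivering the allocated service, and its time points are stated in three incompatible ways.

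If the text is followed as written, the analyst must decide after the fact which reading counts as baseline and whether a six-month contrast exists. A group-by-time result for this outcome could then reflect when and by whom the first reading was taken, and not only the intervention.

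**Working it through.** The plan gives no figure for the ladder. Its only sample-size figure concerns the GHQ-12: effect size 0.50, two-sided alpha 0.05, 80% power. The exact t-test calculation gives 63.77, so 64 per group with power 0.801, as stated. The target of 70 per group leaves room for 1 − 64/70 = 8.6% attrition, close to the stated 10%. None of this depends on the ladder. The rest of the check is a comparison of statements.

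**Step 1. Which points does each statement supply?**

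| Source | Start of service | End of service / T1 | T2 |
|---|---|---|---|
| Needed by the MMRM | yes (as pre-intervention) | yes | yes |
| Table 2 cells | no | no | yes |
| Table 2 footnote | yes (first appointment) | yes (last appointment) | not stated |
| Data collection methods | yes (called baseline) | yes | not stated |

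Service in either arm will not exceed six months (Participant timeline), and T2 is six months after the intervention. The last appointment therefore belongs with T1, not T2. No row below the first supplies all three points.

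**Step 2. Can the first reading be a baseline?** The participant's initial appointment is with the researcher, who obtains consent and gives the questionnaire. The data manager then randomises (Sequence generation and implementation), and the Discussion confirms that assignment follows the baseline assessments. Practitioners serve one arm only, and the footnote has the practitioner collect the ladder. The practitioner's first reading therefore comes after assignment.

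**Step 3. When is it taken?** In controls the first appointment is immediate for Low PEX, within two weeks for Medium, and six months after the group information session for High (Control group section). In the intervention arm, Table 1 has meetings timed by need. The timing rules differ. The actual delays by arm are not given.

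**Step 4. What does this do to a change contrast?** Let D0 be the arm difference in mean ladder score at the first reading and D1 the difference at the end of service. The between-arm contrast in change is

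(mean change, intervention) − (mean change, control) = D1 − D0.

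Randomisation makes D0 zero in expectation only if the reading precedes assignment. If the first session, the allocated practitioner or the wait has already moved scores, D0 is not zero in expectation. The contrast is then too small when D0 has the same sign as D1 and too large when it has the opposite sign. The documents give nothing from which to size D0.

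**Step 5. Can the model repair a missing level?** The plan rightly says that MMRM tolerates different numbers and timings of measurements. That covers participants who miss a visit. It cannot estimate a level at which nobody is measured, or move a post-assignment value to before assignment.

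**The case against.** The strongest reply is that the Table 2 cell and its footnote complement each other: first and last appointment come from the practitioner and T2 from the follow-up visit, which makes three readings and matches the model. This is possible, and the questionnaires are in additional files that are not shown. But the data collection text names only two points, and even on this reading the first value follows randomisation. The reply weakens the six-month part of the concern and leaves the baseline part intact.

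Several stronger readings are tempting but not supported:

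- A reader might infer that no T2 value exists. The Table 2 cell says otherwise; that conclusion holds only if the footnote and data collection text govern.
- A reader might infer that no analysis can be run. Only the three-level model lacks support; a comparison at the points collected is possible.
- A reader might say the model adjusts for a post-randomisation covariate. It does not: the pre-intervention reading is a response level. The damage is to change contrasts, as in Step 4.
- A reader might argue that High PEX controls, first seen at six months, show zero change because first and last appointment coincide. A single reading would leave change missing, not zero, and Table 1 gives controls 3–4 meetings over six months.
- A reader might state as fact that the delay differs between arms. The timing rules differ, but no delays are reported, so this is an inference.

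The ladder is also self-rated; the practitioner administers it and does not score the client. The Blinding section admits that the researcher is unblinded after baseline, so moving the item to the researcher would align collector and timing but not restore blinding.

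**Conclusion.** The point stands as an internal contradiction with an analytic consequence. Table 2, its footnote, the data collection text and the analysis section do not describe one schedule, and no single collection statement supplies the three levels of the model. No reading of the text supplies a ladder value from before randomisation. Depending on which statement governs, the outcome lacks T2, or lacks both T0 and T1, or (on the complementary reading) has three points with a post-assignment first one.

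This rests on two assumptions. The mark in the ladder row of Table 2 is taken to sit under t2 as it appears; other rows keep their empty cells, which supports that. If the mark were misplaced, the footnote and data collection text would still conflict with the model. The first appointment in the footnote is taken to be the practitioner's, because the footnote names the practitioner as collector.

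The scope is one of eight secondary outcomes. The size of any bias cannot be computed from the documents. The primary outcome and the sample size are untouched. The correction should be made before the database is opened.

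**What to change.** 1. Reconcile Table 2, its footnote, Data collection methods and Statistical methods/analysis, so that all state the same ladder time points and collector.
2. Stop labelling the practitioner's first reading as baseline, and take the ladder out of the three-level T0/T1/T2 MMRM.
3. Compare arms at the post-intervention and six-month points actually collected. Adjust only for covariates measured before randomisation: those the analysis section already names and, optionally, the T0 career self-efficacy score. That last choice is a matter of judgement, since the documents give no correlation with the ladder.
4. Report the practitioner's first and intermediate readings descriptively.
5. If still feasible, add the ladder item to the researcher-administered T1 and T2 questionnaires for participants not yet past those visits.

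**Cost.** Steps 1 to 4 are wording changes, which the full SAP promised before database opening can carry. Step 5 adds one item to two existing questionnaires and may need a formal amendment, with approval from the funder, the NGO and the ethics committee (Protocol amendments). No true T0 ladder can be obtained for the 140 already randomised, and some T1 values will be missing.

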### Secondary outcome measures

Data will be collected for eight secondary outcomes (Table 2) which have been shown to benefit the unemployed in terms of mental health and increased employability. *Self-esteem* will be measured by the *Rosenberg Self- Esteem Questionnaire* [63], a ten-item scale designed to measure global self-esteem. *Career self-efficacy* will be measured by the *Career Self-Efficacy Questionnaire* which was adapted by Kossek et al. [64] from Sherer and Adam’s [65] General Self-Efficacy Scale to measure a context-specific form of self-efficacy. This is an 11-item self-report questionnaire which measures an individual’s belief in his or her ability to manage their own career.

*Resilience* will be measured by the *Brief Resilience Scale* [66], a six-item self-report questionnaire designed to assess the ability to bounce back or recover from stress. *Hopefulness* will be assessed using the *State Hope Scale*, a six-item self-report scale which examines goal directed thinking in a given moment [67]. *Perceived progress towards the labour market* will be measured by *Cantril’s Self-Anchoring Ladder* [68], a ten-step ladder where the top of the ladder represents the best possible situation for an individual and the bottom of the ladder represents the worst possible situation. The scale has been used in research as a type of wellbeing assessment and measures wellbeing as defined by judgements of life or life evaluation [69]. However, this scale has been adapted for the current study so that the focus is on career goals and the best and worst possible situation for the individual in relation to their career.

*Re-employment or labour market participation* will be assessed by rates of progression into employment post intervention (T1) and at six-month follow-up (T2). This will be measured by a single item which asks individuals to indicate whether they are ‘currently unemployed’ or ‘currently employed’. The *quality of re-employment* will be assessed in terms of:*Job satisfaction:* single item answered on a 4-point scale (‘All in all, how satisfied would you say you are with your new job?’) [70].*Job sustainability:* single item answered on a 7-point scale (‘How likely is it that you will actively look for another job in the next year?’) [71].Satisfaction with *level of earnings* will be rated on a 5-point scale ranging from ‘very dissatisfied’ to ‘very satisfied’.

*Access to education/vocational training* will be assessed by rates of progression into education and /or training and its relevance to the individual’s career plan post intervention at T1 and at T2. This will be measured by a single item which asks individuals to indicate whether they have completed an education or training course relevant to their career plan, are currently registered on an education or training course relevant to their career plan, are waiting to start an education or training course relevant to their career plan or are not participating in education or training.

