### The current study: objectives

The principal aim of this study (called ‘EEPIC’) is to assess the impact of a newly developed therapeutic career guidance intervention—when compared to routinely available support—on the psychological wellbeing (including hopefulness and resilience) and perceived employability of a sample of long-term unemployed job-seekers in a disadvantaged urban setting. The goal of the intervention is to support the unemployed in strengthening their wellbeing, build hopefulness, resilience and career self-efficacy in order to improve employability, and increase access to sustainable labour market opportunities.

This new high support intervention uses a career/vocational guidance approach and aims to increase levels of psychological wellbeing when compared to current employment support services (Pathways to Work) provided to the long-term unemployed. In terms of ALMPs, the intervention could be categorised within the OCED’s classification as a ‘Job Search Assistance’ programme. A full description of the intervention vs usual services is provided in Table 1. This new high support intervention is designed to: (1) increase levels of wellbeing in the long-term unemployed; and (2) help to improve their employability.

**Table 1 Tab1:** Aspects of service as usual vs intervention

Aspects of service	Service as usual	Intervention
Profile form detailing individual needs and barriers to progression		x
Tailored career guidance process		x
Career plan – with short- and long-term goals (agreed after the guidance process)		x
Stated importance of relationship building between client and practitioner		x
Personal progression plan (agreed at 1st meeting)	x	
Implementation of career plan with support of guidance practitioner		x
Review meetings	x	x
Timing of meetings	Indicated by PEX profiling score	Indicated by need as identified by practitioner/client
Number of meetings	3–4 over 6-month period	3–6 over 6-month period

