## Interventions

### The EEPIC intervention

The new EEPIC intervention is a high-support therapeutic guidance programme which focuses on the development of a career plan and strengthening the human, social and psychological capital required to implement this plan**.** The intervention consists of a four-stage process (see Fig. 2), which typically lasts 8–12 weeks, and which aims to support the job-seeker in developing the skills necessary for labour market access while building self-efficacy and esteem and improving psychological wellbeing:*Stage 1:* The individual’s needs (education, training, skills, personal situation, employment history, perceived employability competencies, work values, barriers to employment, wellbeing, etc.) are assessed using a Profile Form adapted from the Ballymun Youth Guarantee (Ballymun Job Centre, 2013) and EMERGE (Ballymun Job Centre, 2010–2012) initiatives. Identification of specific needs and their severity is vital in understanding the barriers faced by the individual and the types of supports and actions required to enable them to move towards the labour market. The outcome of the individual needs assessment determines the extent to which guidance practitioners may need to support the individual to engage with appropriate services to address issues which pose barriers to progression (e.g. addiction, literacy). Interaction with other services and supports are documented by the practitioner in their case notes.*Stage 2:* A tailored career guidance process is implemented to support the job-seeker in identifying latent skills, abilities, aptitudes, preferred behaviour style in the workplace and values. This process aims to build career clarity, career identity and improve self-esteem and career efficacy. Vocationally orientated career guidance tools and approaches (e.g. career interest inventories, general and specific aptitude assessments, person-centred vocational counselling) are used to reveal hidden strengths, aptitudes and preferences, while limitations are also acknowledged and documented. This information is used to inform the development of a detailed career plan.*Stage 3:* The job-seeker and guidance practitioner work together to develop a career plan which includes a career objective or aspiration, a number of shorter-term career goals which should be SMART (Specific, Measurable, Achievable, Realistic and Time-bound) and potential barriers to progression. A timescale for this plan is also identified and a method to achieve it is discussed, particularly in relation to responsibilities and extent of contact required (e.g. weekly/fortnightly meetings with the guidance practitioner).*Stage 4:* The career plan is implemented in a supportive and positive way. This involves the job-seeker and the practitioner working together to accomplish the planned career goals, to maintain levels of motivation, to build resilience against setbacks and adapt and re-plan as required.

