At this first appointment, the client and case officer agree a number of steps or goals which the client commits to undertake as part of a Personal Progression Plan (PPP). This plan is signed and becomes the client’s responsibility to fulfil. Within the current study, case officers are also required to use the *Cantril’s Ladder* scale at the first appointment to assess the client’s perceived progress towards the labour market.*Step 2:* Case officers decide on and conduct systematic follow-ups (e.g. phone call, email, text) after the first meeting in order to ‘check in’ with the client and to see how they are progressing. The level of contact is normally agreed in the PPP and a follow-up category is set in the Client Services System (i.e. the DSP’s IT database) which calculates when the client is due for systematic follow-up.*Step 3:* The case officers are required to conduct Activation Review Meetings (ARM) by the DSP which can include a phone call or a face-to-face meeting to review progress of the tasks identified and agreed in the PPP. This is essentially a monitoring meeting and the timing of these meetings is dependent on the client’s initial PEX score:‘High PEX’ clients receive an ARM meeting at six months and every three months thereafter;‘Medium PEX’ clients receive an ARM meeting every three months;‘Low PEX’ clients receive an ARM meeting every two months;Under 25 s (High, Medium and Low PEX) receive monthly ARM meetings.

Within the current study, case officers will also be required to use Cantril’s Ladder at the ARM meeting to assess perceived progress towards the labour market.

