In addition, descriptive statistical summaries (means, standard deviations, frequencies) will be presented for primary and secondary outcome measures at each time point (baseline, post intervention and six-month post intervention). Of most interest will be the identification of changes in primary and secondary outcome measures at group level between T0 (baseline) and T1, and T0 and T2, and between T1 and T2. Additional descriptive analysis (e.g. frequencies) of the re-employment (secondary) measure will be conducted to assess the differences between the two groups in terms of their re-employment outcomes.

Sub-group MMRM analysis will be conducted to investigate if the intervention effects differ for certain participant groups, based on variables such as gender, age, education level and unemployment duration. T-tests and Chi-squared tests will be employed to identify mean differences and associations with regard to primary and secondary outcome measures.

A full statistical analysis plan (SAP)—in the form of a Trials (free) update—will be provided once all data are gathered and before opening the database. Analysis will be conducted using SPSS software (IBM SPSS Statistics version 22).

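### The education/training item counts only courses tied to a career plan, which only the intervention arm receives, so it does not measure the two arms equivalently

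*Protocol article*

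**What the plan says.** Protocol article, Secondary outcome measures: access to education and vocational training is measured through "rates of progression into education and /or training and its relevance to the individual’s career plan post intervention at T1 and at T2". One item does this, with four answers. The first is to "have completed an education or training course relevant to their career plan". The second (currently registered) and third (waiting to start) carry the same qualifier. The list closes with a course "relevant to their career plan or are not participating in education or training". No answer fits a course that lies outside a career plan.

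Table 1 (The current study: objectives) has a row "Career plan – with short- and long-term goals (agreed after the guidance process") marked in the intervention column only. The EEPIC intervention section confirms that the programme "focuses on the development of a career plan and strengthening the human, social and psychological capital required to implement this plan". Table 1 marks a personal progression plan for service as usual only, and the Control group section describes it as "steps or goals which the client commits to undertake as part of a Personal Progression Plan (PPP"), agreed at the first appointment.

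In Statistical methods/analysis, the mixed model covers five of the eight secondary outcomes, and training is not one of them. The only test text that could reach it is general: "T-tests and Chi-squared tests will be employed to identify mean differences and associations with regard to primary and secondary outcome measures". The same section says the full SAP will be supplied once all data are gathered and before the database is opened.

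One job-quality item asks "how satisfied would you say you are with your new job"; this and the other two job-quality ratings are listed under quality of re-employment.

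**The concern.** A between-arm outcome should ask the same question of both arms. Here the condition for a positive answer is a document that is a core component of one arm and, by Table 1, absent from the other. Uptake of training and relevance to the plan are also merged in one answer, so the uptake rate cannot be recovered from the item afterwards. Two arms entering training at the same rate could report different rates because of the wording alone.

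This is not a matter the SAP can fully settle. It will be written after the answers have been recorded, and no analysis can separate a control participant who is truly out of training from one on a course who found no fitting answer.

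At stake is a named secondary outcome that bears on the stated goal of access to sustainable labour market opportunities. The primary outcome, the sample size and the mixed-model analyses are not affected.

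**Working it through.** **The plan's own figures.** The article gives no rate, effect size or power for the training outcome. Its sample size (64 per group for a standardised difference of 0.50, 80% power, two-sided 5%) concerns the GHQ-12. It reproduces (63.8, rounded up to 64) but has no bearing on this point.

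**The item against what each arm receives.**

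| True situation | Intervention arm (career plan) | Control arm (Personal Progression Plan) |
|---|---|---|
| On a course that fits the participant's plan | Positive option fits | Fits only if the progression plan is read as a career plan |
| On a course outside any plan | No option fits | No option fits |
| Not in training | Last option fits | Last option fits |

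The first row differs by arm.

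**Illustration of size.** Every rate here is an assumption.

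- Sample: 70 per group less 10% attrition, 70 × 0.9 = 63 per arm.
- True uptake u = 30% in both arms, so there is no true effect.
- Share of true trainees who give a positive answer: a_I in the intervention arm, a_C in the control arm.
- Observed rates: p1 = u × a_I and p0 = u × a_C. Spurious difference d = p1 − p0.
- Probability of a result favouring the intervention at two-sided 5%: Φ[(d − 1.96 × SE0)/SE1], where SE0 = √(2p̄(1 − p̄)/63), SE1 = √(p1(1 − p1)/63 + p0(1 − p0)/63) and p̄ is the mean of p1 and p0.

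With a_I = 1:

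- a_C = 1 (controls answer by their own plan): 30% v 30%, d = 0, rejection at the nominal 5%.
- a_C = 0.75: 30% v 22.5%, d = 7.5 points, SE0 = 0.0784, SE1 = 0.0781. (0.075 − 0.1537)/0.0781 = −1.01, giving 15.7%.
- a_C = 0.50: 30% v 15%, d = 15 points, SE0 = 0.0744, SE1 = 0.0732. (0.150 − 0.1458)/0.0732 = 0.06, giving 52.3%.

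**Other assumptions.** With 64 per arm, a_I = 0.9 and true uptake between 20% and 50% in both arms:

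| Share counted in controls | Spurious difference | Probability of rejection |
|---|---|---|
| 90% | 0 | 5% |
| 70% | 4 to 10 points | 9% to 21% |
| 50% | 8 to 20 points | 26% to 66% |
| 0% | 18 to 45 points | 95% to nearly 100% |

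**Opposite direction.** If intervention participants leave out off-plan courses while controls count any course (a_I = 0.75, a_C = 1), the calculation is symmetric: −7.5 points and about 16%.

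**Job quality, for contrast.** Suppose there is no effect on quality, and re-employment depends on a latent trait with correlation ρ to quality. The bias among the employed is then ρ × [m(e1) − m(e0)] in SD units, where e1 and e0 are the re-employment rates in the intervention and control arms and m(e) = φ(z)/e, with z the upper-e point of the standard normal. At equal rates, or with ρ = 0, it is zero. At 30% v 20% it is −0.07 (ρ = 0.3) to −0.12 (ρ = 0.5). At 50% v 20% it is −0.18 to −0.30. In this model the bias, when present, runs against the intervention.

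**The case against.** The strongest reply is that controls may not read the term as the Table 1 document. They have a signed plan with agreed goals, and the Blinding section says participants do not know their allocation, so they may not know that they lack a formal career plan. A participant answering from personal goals would use the positive options freely, and then there is no bias. This stands: the direction is probable, not certain, and the size cannot be fixed from the article. It does not rescue the item, because nothing in the article tells controls to read it that way.

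A second reply is that the article only describes the item. The questionnaires are in additional files not shown, and under Data collection methods the update questionnaire covers training progression and the tracking file holds outcome updates. Data on training free of the plan condition may therefore exist. This also stands in part and is the basis for recoding earlier forms. The update questionnaire may, however, carry this same item, in which case recoding from it would be circular.

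A reader might also infer that the job-quality comparison is biased by construction, since those ratings exist only for people who found work. The documents do not support that. Such a comparison is not protected by randomisation, but bias needs the arms to differ in who is placed, together with a link between employability and job quality, and it can go either way. The article also fixes no job-quality contrast: these ratings are in neither the null hypothesis nor the mixed model, and the general sentence on t-tests and chi-squared tests follows directly on the subgroup plan. How participants without a job are handled can be left to the SAP.

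**Conclusion.** The point holds for the training item. Its definition depends on a component of one arm, it has no answer for training outside a career plan, and it cannot yield a comparable uptake rate. A spurious difference is possible and more likely to favour the intervention.

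Under the stated assumptions (30% true uptake in both arms, 63 per arm), the effect runs from none, if controls answer by their own plan, to a false gap of 7.5 to 15 points with about 16% to 52% rejection, if 25% to 50% of control trainees say they are not participating. These percentages illustrate the mechanism. The article supplies neither the uptake nor the misreporting rate.

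It should be corrected as a fault in a secondary outcome. For job quality, a descriptive label on any between-arm comparison is enough.

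**What to change.** 1. For the remaining T1 and T2 visits, ask both arms the same unqualified question: completed, registered on, waiting to start, or not in any education or training. Use this as the between-arm outcome.
2. Record relevance to the career plan in a separate question and report it as description only.
3. For forms already returned, recode from the tracking file's outcome updates where these allow. Do this blind to arm if possible. The researcher who keeps the file knows the allocation after baseline, and the file names the practitioner, who serves one arm only. A second person working from an extract without that column would be preferable.
4. Report how many forms at each visit used each wording or were recoded.
5. State in the SAP that comparisons of job satisfaction, job sustainability and satisfaction with earnings among the re-employed are descriptive.

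Cost: all 140 participants are already randomised, so the rewording reaches only the visits still to come; the article does not say how many. Because it changes an outcome, the Protocol amendments section would require a formal amendment approved by the funder, the NGO and the ethics committee. Item wording will be mixed across visits, and some early forms may not be recodable.
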